The mean ( $\pm$ SD) angiomyolipoma volume at 12 months was 53.2 $\pm$ 26.6% of the baseline value ( $P < 0.001$ ) and at 24 months was 85.9 $\pm$ 28.5% of the baseline value ( $P = 0.005$ ). At 24 months, five patients had a persistent reduction in the angiomyolipoma volume of 30% or more. During the period of sirolimus therapy, among patients with LAM, the mean FEV1 increased by 118 $\pm$ 330 ml ( $P = 0.06$ ), FVC increased by 390 $\pm$ 570 ml ( $P < 0.001$ ), and the residual volume decreased by 439 $\pm$ 493 ml ( $P = 0.02$ ), as compared with baseline values. One year after sirolimus was discontinued, the FEV1 was 62 $\pm$ 411 ml above the baseline value, the FVC was 346 $\pm$ 712 ml above the baseline value, and the residual volume was 333 $\pm$ 570 ml below the baseline value; cerebral lesions were unchanged. Five patients had six serious adverse events while receiving sirolimus, including diarrhea, pyelonephritis, stomatitis, and respiratory infections.

The authors noted that although angiomyolipoma regressed during sirolimus therapy, they tended to increase in volume after the therapy was stopped. Some patients with LAM had improvement in spirometric measurements and gas trapping that persisted after treatment. Lung function in patients who did not have LAM was not reported. The authors concluded

that suppression of mTOR signaling might constitute an ameliorative treatment in patients with the TSC or sporadic LAM.

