## 5.1 Inclusion criteria

1. Male or female  $\geq 18$  years of age.
2. Clinically definite diagnosis of tuberous sclerosis according to the modified Gomez criteria ([Roach 1998](#), [Hyman 2000](#), [Table 5-1](#)) **or** sporadic LAM (biopsy-proven or compatible chest CT scan). Clinically definite diagnosis of tuberous sclerosis according to the modified Gomez criteria is defined as either of the following:
  - Two Major Features from Table 5-1.
  - One Major Feature plus two Minor Features from [Table 5-1](#).
3. Clinically definite diagnosis of renal angiomyolipoma.
4. Presence of at least one angiomyolipoma  $\geq 3$  cm in its longest diameter using CT/MRI.
5. If female and of child-bearing potential, documentation of negative pregnancy test prior to enrollment. Sexually active pre-menopausal female patients (and female partners of male patients) must use highly effective contraceptive measures, while on study and for 8 weeks after ending treatment.
6. Written informed consent according to local guidelines.

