- an increase from nadir of 25% or more in angiomyolipoma volume to a value greater than value just prior to everolimus starting date (where angiomyolipoma volume is the sum of the volumes of all target angiomyolipomata identified prior to everolimus start and where nadir is the lowest angiomyolipoma volume achieved by the patient previously in the everolimus period (including the value just prior to everolimus starting date))
- an increase from nadir of 20% or more in the volume of either kidney to a value greater than value just prior to everolimus starting date, where nadir is the lowest kidney volume obtained for the patient, separately for each kidney, previously in the everolimus period (including the value just prior to everolimus starting date)
- the appearance of a new angiomyolipoma  $\geq 1.0$  cm in longest diameter
- angiomyolipoma-related bleeding grade  $\geq 2$  as defined by NCI CTCAE, version 3.0.

In addition, if most patients have small AML lesions (less than 1 cm) at the end of everolimus treatment, the sum of the angiomyolipoma target lesions volume identified at the end of

everolimus treatment with a diameter greater than 1 cm will be described at the time of everolimus discontinuation and at the one-year follow-up scan. The change and percentage change in volume from the time of everolimus discontinuation will also be presented.

If the number of patients included in this analysis is sufficient, the angiomyolipoma progression rate 1-year following everolimus discontinuation will be provided with exact 95% confidence intervals (Clopper and Pearson 1934). The angiomyolipoma progression following everolimus discontinuation will be defined as one or more of the following:

- an increase of 25% or more in angiomyolipoma volume from the end of everolimus treatment (where angiomyolipoma volume is the sum of the volumes of target angiomyolipomata identified as greater than 1 cm at the time of everolimus discontinuation)
- an increase of 20% or more in the volume of either kidney from the end of everolimus treatment
- the appearance of a new angiomyolipoma  $\geq 1.0$  cm in longest diameter
- angiomyolipoma-related bleeding grade  $\geq 2$  as defined by NCI CTCAE, version 3.0.

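### In 10.5.11 the only progression rate measured from the end of everolimus appears to depend on an undefined small-lesion trigger, and its volume sum leaves out the small lesions

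*Protocol*

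**What the plan says.** Section 6.7.8 gives the aim of the non-interventional follow-up: to characterise angiomyolipoma for up to a year after everolimus is stopped for good. Section 10.5.11 sets the analysis in three parts.

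- **Description, no lesion-size condition.** Change and percentage change in the summed volume of the target lesions identified before everolimus, measured from the start and from the end of everolimus, with individual plots and similar analyses for kidney volume.
- **Rate A, following Section 7.5.2.** Its lesion criterion is "an increase from nadir of 25% or more in angiomyolipoma volume to a value greater than value just prior to everolimus starting date". Its kidney criterion has the same form, with a 20% threshold that must also pass the pre-everolimus value. A new lesion of at least 1.0 cm or bleeding of grade 2 or worse also counts.
- **Rate B, from the end of everolimus.** A further paragraph applies "if most patients have small AML lesions (less than 1 cm) at the end of everolimus" treatment. It limits its description to the larger lesions, in the words "everolimus treatment with a diameter greater than 1 cm will be described at the time of everolimus discontinuation and at the one-year follow-up scan". A second rate follows: a 25% volume rise from the end of everolimus, summed over "target angiomyolipomata identified as greater than 1 cm at the time of everolimus discontinuation", or a 20% rise in either kidney from the end of everolimus, or a new lesion, or bleeding.

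Both rates carry exact 95% confidence intervals and are given only if enough patients are in the analysis.

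**The concern.** Rate B is the only progression rate that takes the end of everolimus as its reference, which is the question this phase asks. Two features of its wording get in the way.

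First, by position and by its repeated lesion restriction, Rate B belongs to the paragraph opened by the small-lesion trigger. The trigger does not say whether all of a patient's lesions, the largest, or any one of them must be under 1 cm. Whether Rate B appears can therefore be settled after the data are seen.

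Second, the volume criterion omits the lesions that set the trigger. It is invoked because lesions have become small, and it then sums only those that have not.

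If the trigger is not met, only Rate A remains. Under Rate A's volume criteria a patient who regrows most of what was lost, but stays below the pre-everolimus value, has not progressed. The protocol itself reports, for sirolimus, that "they tended to increase in volume after the therapy was stopped", so partial regrowth is the pattern to expect.

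**Working it through.** Section 10.5.11 states no expected rate, power or sample size, so there is no planned figure to reproduce. The checks below apply its rules to figures elsewhere in the protocol.

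**Inputs**
- Sirolimus phase II (sections 1.2 and 1.4.7): mean volume 53.2% of baseline (SD 26.6) at 12 months, when drug stopped, and 85.9% (SD 28.5) at 24 months. Of 25 enrolled, 20 and 18 completed the two evaluations.
- RAD001 phase II (section 1.4.6): 12-month reductions in summed target volume of 12.8% to 67.5% in 9 patients.
- Eligibility (section 5.1): "Presence of at least one angiomyolipoma" of 3 cm or more.

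**1. A patient at the sirolimus means**
- Rise from stopping: 85.9/53.2 − 1 = 61%. This exceeds Rate B's 25% threshold.
- Level reached: 85.9%, below 100%. Rate A's volume criterion is not met.
- Rise needed to return to the pre-treatment volume is 100/v − 1, where v is the stopping volume as a percentage of it: 88% for v = 53.2, 100% for v = 50, and 208% for v = 32.5 (the 67.5% reduction).

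**2. Proportions of patients**

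Let V12 and V24 be the volumes at stopping and one year later, as percentages of baseline, with the means and SDs above. I drew them as bivariate normal and as log-normal, with an assumed correlation of 0.2 to 0.8 because the protocol gives none. The nadir is the smaller of V12 and 100.

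| Criterion | Normal | Log-normal |
|---|---|---|
| Rise from stopping: V24 ≥ 1.25 × V12 | 68-83% | 73-86% |
| Rate A volume: V24 ≥ 1.25 × nadir and V24 > 100 | 28-29% | 23-24% |

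The normal column includes the draws limited to positive volumes. Overall the first row spans 68-86% and the second 23-29%. As a cross-check, the normal tail above 100 alone is 1 − Φ((100 − 85.9)/28.5) = 31%. It is slightly higher because it does not also require the 25% rise.

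**3. Can the trigger be met?** (spheres, so volume is proportional to diameter cubed)
- From 3 cm to 1 cm: 1 − (1/3)³ = 96.3% volume loss.
- The largest cited reduction, 67.5%, takes 3 cm to 3 × 0.325^(1/3) = 2.06 cm.
- Small targets can cross: 1.25 cm needs 1 − (1/1.25)³ = 49%, and 1.5 cm needs 70%.

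If the trigger concerns each patient's largest lesion, it looks hard to meet on these data. If it concerns any target, it could readily be met.

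**4. How much does the omission matter?**
- A target regrowing from 0.96 to 1.4 cm goes from 0.46 to 1.44 mL, a factor of (1.4/0.96)³ = 3.1. It is outside Rate B's sum and is not plainly a new lesion.
- A 3 cm lesion (14.14 mL) at 53.2% of its volume is 7.52 mL. Including the small target would raise that patient's sum by (1.44 − 0.46)/(7.52 + 0.46) = 12%, which alone is short of 25%.

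**5. Kidney criterion as a backstop**

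The protocol gives no kidney volume, so I assume 150 to 500 mL. A lesion growing from 0.9 to 2 cm adds (π/6)(2³ − 0.9³) = 3.81 mL. A 20% kidney rise (30 to 100 mL) then needs about 8 to 26 such lesions. The criterion picks up large regrowth of omitted lesions, but not modest regrowth.

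**The case against.** The strongest reply is that regrowth is already reported. Section 10.5.11 describes percentage change from discontinuation on all pre-everolimus targets, with plots, whatever the lesion size. Rate A is the trial's own Section 7.5.2 definition, and keeping it is defensible. Both rates are descriptive, untested, and come from a subset whose selection biases the protocol acknowledges. The 1 cm cut matches the trial's measurability rule. All of this stands, and it limits the weight of the point. It does not supply a progression proportion, with interval, measured from stopping.

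A second reply is that the small-lesion clause is not printed on the Rate B sentence, whose own condition is a sufficient number of patients. That is correct. The link rests on context, which is why it is described here as apparent. If Rate B was meant to be unconditional, the text should say so, and the omission of small lesions would remain.

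A reader might go further in three ways that the document does not support.
- *Regrowth after stopping is never counted as progression.* Rate B counts growth of lesions above 1 cm and a 20% kidney rise from the end of everolimus. Rate A counts regrowth past the pre-everolimus value. Both count new lesions and bleeding.
- *The trigger can never be met.* That extrapolates 12-month data from 9 patients to people who may have had four years of treatment, and it assumes one reading of the trigger.
- *Rate B breaks down because patients with every target at or below 1 cm have no volume to compare.* Such a patient would indeed have none. But the same shrinkage data that make the trigger look hard to meet make this patient unlikely, so the two arguments cannot both be pressed.

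Nor do Rate A and the descriptive changes contradict each other. They answer different questions.

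**Conclusion.** The point holds as a drafting weakness in a descriptive analysis. On the natural reading, the one progression rate referenced to the end of everolimus depends on an undefined, data-dependent trigger, and its volume criterion omits the lesions that set that trigger. If the trigger is not met, the only rate reported is one whose volume criteria do not count regrowth staying below the pre-everolimus value.

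On the sirolimus moments, about 68-86% of patients would show at least a 25% rise from stopping, against roughly 23-29% meeting Rate A's volume criterion. This is illustrative: a different drug, about 20 patients, an assumed distribution and correlation, and the lesion-volume component only. The gap comes mainly from the choice of reference point. Leaving out lesions of 1 cm or less has a smaller effect, about 12% of the sum in the example. The primary and main secondary conclusions are not affected.

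**What to change.** In section 10.5.11:

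1. Keep the Section 7.5.2-type rate as it is.
2. Remove the small-lesion trigger, so that the rate referenced to the end of everolimus is always reported alongside it, subject to the same sufficient-number condition.
3. Compute that rate's lesion criterion on the sum of all target lesions identified before everolimus. The section already requires this sum at both time points.
4. State a rule for stopping volumes at or near zero, where a 25% rise is undefined or trivial.
5. Report the version restricted to lesions above 1 cm at discontinuation as a sensitivity analysis.

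The cost is a wording change and one more table, with no new scans. The drawback is that volumes of lesions below 1 cm are measured with more noise, though they contribute little to the sum.

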## 10.6 Interim analysis

No interim analysis is planned for this study.

## 10.7 Sample size calculation

The primary analysis compares angiomyolipoma response rate between the two treatment arms using an exact Cochran-Mantel-Haenszel test (Agresti 2002) in the Full Analysis Set. The randomization is unbalanced, with two patients allocated to RAD001 for every one patient allocated to placebo. In addition, the randomization is stratified by one factor with three categories: (1) TSC as underlying disease and patient using EIAED at randomization, (2) TSC as underlying disease and patient not using EIAED at randomization, and (3) sporadic LAM as underlying disease. It is anticipated that about 75% of patients will have TSC (of the 25 enrolled patients in the recent trial reported by Bissler et al (2008), a total of 19 (76%) had TSC and 6 (24%) had sporadic LAM) and, of the TSC patients, about half are expected to be using EIAED at the time of randomization. That is, the relative prevalence of the categories (1) to (3) of the stratification factor is expected to be 3:3:2. It is planned to use a one-sided test and a 2.5% significance level. The angiomyolipoma response rate in the placebo arm is expected to be close to 0%, since there are no reported cases of spontaneous tumor regression in patients with angiomyolipoma. The angiomyolipoma response rate on RAD001 is anticipated to be at least 20%.

Sample size was determined using simulation (note that software providing sample sizes for exact CMH tests with unbalanced randomization is not readily available). The simulation approach involves randomly generating data according to the study assumptions for a large number of simulated trials, and then analyzing each trial using the exact CMH test. The proportion of times that the test is significant (i.e., has a one-sided p-value  $\leq 0.025$ ) gives the study power. Different sample sizes can be assessed, and by trial and error a sample size that guarantees a study power of at least 90% can be chosen. As a starting value, NQuery (V4.0) indicates that for analysis using Fisher's exact test (i.e., a different exact test, and one that

does not take into account the stratification), a total of 99 patients would provide 93% power (2:1 randomization).

The power of the exact CMH test with 99 patients is shown in Table 10-2 below according to the study assumptions, notably a fixed overall angiomyolipoma response rate on RAD001 of 20%, and assuming a 3:3:2 ratio in the number of patients in Stratum 1 (TSC and use of EIAED) versus Stratum 2 (TSC and non-use of EIAED) versus Stratum 3 (sporadic LAM). The row in the table in bold assumes no treatment by stratum interaction; other rows show differing levels of interaction, where at the extreme the angiomyolipoma response rate is assumed to be 0% in one of the strata. As can be seen, the power of the stratified test is highly robust to even the most extreme treatment by strata interaction. The sample size of 99 patients provides at least 93% power in all cases considered.

**Table 10-2 Sensitivity of study power to treatment by stratum interaction assuming 3:3:2 ratio of patients across strata 1-3**

| Ratio of patients across strata 1-3 | Angiomyolipoma response rate in RAD001 arm |                               |                          |            | Power*        |
|-------------------------------------|--------------------------------------------|-------------------------------|--------------------------|------------|---------------|
|                                     | Stratum 1 (TSC with EIAED)                 | Stratum 2 (TSC without EIAED) | Stratum 3 (sporadic LAM) | Overall    |               |
| 3:3:2                               | 26.67%                                     | 26.67%                        | 0%                       | 20%        | 93.20%        |
|                                     | 20%                                        | 33.33%                        | 0%                       | 20%        | 93.53%        |
|                                     | 23.33%                                     | 23.33%                        | 10%                      | 20%        | 93.56%        |
|                                     | 16.67%                                     | 30%                           | 10%                      | 20%        | 93.48%        |
|                                     | 20%                                 | 20%                    | 20%               | 20% | 93.30% |
|                                     | 10%                                        | 30%                           | 20%                      | 20%        | 93.37%        |
|                                     | 13.33%                                     | 13.33%                        | 40%                      | 20%        | 94.09%        |
|                                     | 6.67%                                      | 20%                           | 40%                      | 20%        | 93.68%        |
|                                     | 0%                                         | 0%                            | 80%                      | 20%        | 98.50%        |

\*Based on 10000 runs, and assumes 66/33 patients on RAD001/Placebo, Placebo response=0%, one-sided exact CMH test at 2.5% level.

The power of the exact CMH test is also highly robust to the assumption of a 3:3:2 ratio in the number of patients across the strata 1-3. For example, consider the case where only 10% of the randomized patients had sporadic LAM: then the relative prevalence of categories 1-3 of the stratification factor would be 4.5:4.5:1. In addition, if only a third of the randomized patients with TSC were taking EIAED at randomization, the relative prevalence of the stratification categories 1-3 would become 3:6:1. Simulations have been run with these (and other) ratios of patients to strata 1-3, and in all cases the study power was maintained at 93% or higher. The power was maintained for varying degrees of treatment by stratum interaction.

Table 10-3 shows the relationship between study power and the size of the treatment effect. The power is rather sensitive to even small changes in the RAD001 response rate; however, with 99 patients the power is at least 86% if the true angiomyolipoma response rate is greater than 18%, and at least 97% if it is greater than 22%. The required increase in sample size to provide sufficient power to detect smaller treatment effects was considered unnecessary (e.g., if the true response rate on RAD001 was 14%, sample size would need to increase by about 35% in order to ensure 90% power).

**Table 10-3 Sensitivity of study power to size of treatment effect**

| Angiomyolipoma response rate |         | Power* with 99 patients | Number of patients to ensure ≥90% power* |
|------------------------------|---------|-------------------------|------------------------------------------|
| RAD001                       | Placebo |                         |                                          |
| 14%                          | 0%      | 58.76%                  | 135                                      |
| 16%                          | 0%      | 75.29%                  | 117                                      |
| 18%                          | 0%      | 86.52%                  | 105                                      |
| 20%                          | 0%      | 93.30%                  | 96                                       |
| 22%                          | 0%      | 97.02%                  | 87                                       |
| 24%                          | 0%      | 98.76%                  | 78                                       |
| 26%                          | 0%      | 99.50%                  | 72                                       |

\*Based on 10000 runs, and assumes 2:1 ratio for RAD001:Placebo, 3:2:2 ratio for Stratum 1:Stratum 2:Stratum 3, one-sided exact CMH test at 2.5% level.

Taking all these simulation results into account, the total sample size was chosen to be 99 patients, with 66 randomized to RAD001 and 33 randomized to placebo.

## 11 Administrative procedures

### Regulatory and ethical compliance

This clinical study was designed and shall be implemented and reported in accordance with the protocol, the ICH Harmonized Tripartite Guidelines for Good Clinical Practice, with applicable local regulations (including European Directive 2001/20/EC and US Code of Federal Regulations Title 21), and with the ethical principles laid down in the Declaration of Helsinki.

### Responsibilities of the investigator and IRB/IEC/REB

The protocol and the proposed informed consent form must be reviewed and approved by a properly constituted Institutional Review Board/Independent Ethics Committee/Research Ethics Board (IRB/IEC/REB) before study start. A signed and dated statement that the protocol and informed consent have been approved by the IRB/IEC/REB must be given to Novartis before study initiation. Prior to study start, the investigator is required to sign a protocol signature page confirming his/her agreement to conduct the study in accordance with these documents and all of the instructions and procedures found in this protocol and to give access to all relevant data and records to Novartis monitors, auditors, Novartis Clinical Quality Assurance representatives, designated agents of Novartis, IRBs/IECs/REBs and regulatory authorities as required.

### Informed consent

Eligible patients may only be included in the study after providing written (witnessed, where required by law or regulation), IRB/IEC/REB-approved informed consent, or, if incapable of doing so, after such consent has been provided by a legally acceptable representative of the patient. Informed consent must be obtained before conducting any study-specific procedures (i.e., all of the procedures described in the protocol). In cases where the subject's legally acceptable representative gives consent, the subject (e.g., minors, patients with severe dementia), should be informed about the trial to the extent compatible with the subject's

understanding and if capable, the subject should assent, sign and personally date the written informed consent. The process of obtaining informed consent should be documented in the patient source documents. In emergency situations when prior consent of the subject is not possible and the subject's legally acceptable representative is not available, enrollment of the subject should require measures described in the protocol with documented favorable opinion of the IRB/IEC/REB. The subject or the subject's legally appointed representative should be informed about the trial as soon as possible and consent to continue and other consent as appropriate should be requested.

A proposed informed consent form that complies with the ICH GCP guideline and regulatory requirements and is considered appropriate for this study is provided to each site. Any changes to the proposed consent form suggested by the investigator must be agreed to by Novartis before submission to the IRB/IEC/REB, and a copy of the approved version must be provided to the Novartis monitor after IRB/IEC/REB approval.

